### 2.4 Participants and recruitment

The design of the efficacy study is a cluster-controlled randomized trial to compare an intervention group (n = 36 classes in which the intervention is carried out) and a control group (n = 36 classes without intervention). These 72 second and third year junior secondary school classes are distributed as follows: 40 in Montpellier and 32 in Dijon. The population consists students aged between 12 and 14 years. In Occitanie, only secondary schools in the Gard and Herault departments took part in the study. Herault has 81 public secondary schools and 29 private secondary schools under contract, i.e. 110 establishments. Gard has 69 public secondary schools and 29 private secondary schools under contract, for a total of 98 establishments. At the start of the 2022 academic year, the Dijon academy (4 departments) have 158 public secondary schools and 24 private secondary schools under contract, for a total of 182 establishments. Secondary schools in the Nièvre, Côte d’Or and Soâne et Loire departments are those taking part in Epidaure Market. The last department could not be represented. To this end, all schools will be geolocated using their exact address, in order to identify the IRIS (Ilots Regroupés pour l’Information Statistique [grouped plots for statistical information]) to which they are attached. The IRIS is the basic unit for the dissemination of sub-municipal statistics, and represents a partition of the territory of these communes into "neighborhoods" with a population of around 2,000 inhabitants. The level of deprivation of the IRIS will then be assigned using the French European Deprivation Index (F-EDI) [58]. Due to school mapping, we assume that the IRIS deprivation level of the schools reflects the deprivation level of the children’s living areas, which is also assessed at the individual level. This approach has already been used in studies of the European adolescent health survey HBSC, Health Behaviour in School-Aged Children [59].

Participants for the Epidaure Market must (i) be students aged between 12 and 14 years, (ii) 5th and 4th grades, (iii) whose parents have agreed to answer the questionnaires, (iv) and have the student’s consent.

### 2.5 Randomisation

Participating classes meeting the inclusion criteria is randomized by the research teams to either the experimental group (EG) or the control group (CG). The science teacher will be the same for both experimental and control classes. It is a stratified randomization by college, with a balance between experimental and control classes. The first knowledge assessment phase (T0) will be carried out before the prevention activity. Each participant will create a participant code (based on the first three letters of their first name, followed by the first two letters of their last name, followed by the name of their middle school and class) to enable anonymous longitudinal correspondence between the 3 measurement/evaluation points.

### 2.6 Intervention

Epidaure Market is a virtual supermarket. The visual display with the different aisles, gondola heads, promotional offers, micro-announcements, etc. and the atmosphere has been designed to recall the actual experience of shopping in a supermarket and to submit the user to the current marketing methods. Users make their purchases on a screen (computer or tablet with or without touch screen) by moving around the aisles of the virtual supermarket. A cash receipt may be printed at the end of the game session to analyze the purchase choices. In addition, the receipt lists the marketing techniques used (e.g. health claims, promotions, packaging) and the price of each item, and the total cost. The first version of Epidaure Market (v1.0) was tested with 261 young people aged from 12 to 18 years. This study showed that this intervention significantly increases the knowledge of marketing techniques and promotes awareness of the influence of marketing techniques and advertising on the consumer choices, including those with potential health impacts [60]. In 2019, this tool was adapted to integrate sustainable food elements in order to increase sustainable consumption choices. Epidaure Market v2.0 is now available on tablet or computer via a site that was specifically developed for classroom use and that provides access to product labels (e.g. nutritional information, Nutri-Score, carbon footprint) (Fig 2).

**Fig 2 pone.0306781.g002:**
[figure not shown]
Example of the information given on food labels.

The Epidaure Market v.2.0 intervention is a school action adapted to the science curriculum and delivered by the Life and Earth Sciences teacher for 4th and 5th graders. The intervention targets 5th and 4th graders, as food is part of the initial curriculum at this age. It is carried out over three sessions (discover, experience and become an actor) based on the serious game, with an extra-curricular session at home, that consists in an exercise involving parents to discuss familial food habits. Details of the sessions can be found in the article by Lecêtre and colleagues [61]. The content of the intervention is schematized in the Fig 3.

**Fig 3 pone.0306781.g003:**
[figure not shown]
Content of the intervention.

Each videogame session targets the students’ motives of sustainable food choices, self-efficacy, and knowledge of sustainable diet, while considering the influence of marketing and sale techniques by the food industry and supermarkets.

#### 2.6.1 Experimental group

Classes assigned to the experimental group will take part in the three Epidaure Market sessions. During these sessions, students, in pairs, shop according to a scenario predefined by the teacher (shopping for a picnic and a snack; a list of pre-tested scenarios is available on the website), with a budget of 8 euros per person. These purchases will then serve as a basis for comparison and analysis of choices during subsequent sessions. The sessions are designed around the BCTs, with the aim of influencing the motives behind teenagers’ food choices (Table 1). The full list of BCTs mobilized can be found in the development article.

**Table 1 pone.0306781.t001:** BCTs mobilized for each session.

	Educational Objectives	Examples of BCTs mobilized
Session 1: Introduction	1. To learn how to read price information and to learn how to compare prices; 2. To learn how to read a product label, especially in relation to the product nutritional values and sustainability; 3. To understand the Nutri-Score meaning; 4. To introduce the concepts of processed and ultra-processed food, raw and fresh products; 5. To learn how to read information about additives; 6. To raise awareness of the product origin; 7. To understand the meaning of ‘eating local’; 8. To learn how to identify the main marketing techniques.	9.1. Credibility of sources: teacher leads in a school context 4.2. Information on behavioural determinants and antecedents
Session 2: Deepening (adaptability session)	1. Learning about the different components of sustainable food 2. Marketing techniques 3. Set up 2 groups for shopping "good for health" or "good for the planet". 4. A product search task at home allows parents to be included in the intervention.	4.1. Instructions for performing the behavior 6.1. Behavior demonstration 5.1. Provide information on the health effects of the behavior 5.2. Highlighting the consequences of the behavior 8.1. Practice and repeat the behavior
Homework: Transferability	1. Knowledge transfer on everyday products 2. Introduce a discussion with parents	6.3. Information on the approval of others 8.1. Practice and repetition
Session 3: Debriefing (Knowledge Enhancement)	1. Feedback on the in-house task 2. Last buying session and comparison with session 1	6.2. Social comparison 8.1. Practice and repetition 8.7. Graduation of actions 2.2. Informing a person about their behavior

Evaluation sessions take place before the sessions (T0), one month after (T1) and 4 to 6 months after the intervention (T2). They are used to assess by questionnaires the effectiveness of the intervention, based on food choice motives, social norms, the ability to choose healthy foods and nutritional qualities or environmental impact.

Student volunteers will also take part in focus groups to discuss obstacles and levers, and assess the acceptability of the intervention. Parents will also be invited to take part in a telephone interview to answer questions on the same themes.

#### 2.6.2 Control group

Classes assigned to the control group will not have access to Epidaure Market sessions before the end of the research evaluation. They will complete all three evaluation sessions (T0, T1 and T2). Depending on their teachers, control groups could benefit of Epidaure Market intervention and use the website after the T2 evaluation session.

### 2.7 Outcomes

#### 2.7.1 Primary outcome measure

The intervention effectiveness will be assessed by comparing the proportion of students who improved their post-intervention parameters in the intervention and control groups. We chose motives for food choices because the intervention improves knowledge and motivation. Indeed, food choice motives are a key factor for changing towards sustainable behaviours [41–44, 46] and a measurement tool is available through a teen-friendly version of the questionnaire by Sautron and colleagues [62]. The questionnaire consists of 104 items divided into four categories: environmental, health and well-being, economic and miscellaneous (i.e. seasonal production, local production, etc.). The questionnaire used for this study had to be adapted to contain fewer items (28 items) and to fit in with the other questionnaires. The environmental, ethical, health and economic categories were included. All items are assessed with four-point Likert-type response scale, concerning their agreement with the stated sentence: 0-not at all agree; 1-strongly disagree; 2- quite agree; 3-strongly agree. A "don’t know" response is also possible if the student doesn’t know the word or concept evoked by the question. This questionnaire on food choice motivations is currently being validated. A factor analysis highlights a general factor: sustainable food, which will therefore be used as the primary outcome. Four secondary factors also emerge from the factor analysis and can be subdivided as follows: importance of ethics, environmental impact, locality and importance of health and absence of toxic substances. They can be used as outcomes in secondary analyses. Validation of the questionnaire will be the subject of another article.

#### 2.7.2 Secondary outcome measure

Social norms will be evaluated by self-assessment following the recommendations by Ajzen et al. [63] with six questions on perceived descriptive norms (*in general*, *my parents make healthy food purchases*) and six questions on perceived injunctive norms (*my friends think I should pay attention to the techniques that push me to buy when I shop for food*). All items are assessed with four-point Likert-type response scale, concerning their agreement with the stated sentence: 0-not at all agree; 1-strongly disagree; 2- quite agree; 3-strongly agree. A "I don’t know" response is also possible if the student doesn’t know the word or concept evoked by the question.

The Personal Efficacy Questionnaire for Eating Healthy Foods [64] will be used to assess the confidence in judgment to achieve a health outcome and confidence in the ability to choose healthy foods.

Nutrition knowledge will be assessed with a product selection task used in the ‘Opticourses’ intervention [65]. This task consists in presenting two food products that are relatively similar, but differ in some criteria, in our case nutritional qualities (Nutri-Score) or environmental impact (origin, label, season). Participants must choose which product is the best according to the available information.

#### 2.7.3 Evaluation of implementation and transferability

*Process analysis and elements of implementation*. The process analysis and conditions for implementation will be assessed using a qualitative study involving the main stakeholders (students, teachers, supervisory staff, parents). An interview guide based on the available literature has been created by the research teams to enable focus groups with pupils, semi-structured individual interviews with teachers, parents and supervisory staff (Table 2).

**Table 2 pone.0306781.t002:** Example of axes for process & transferability evaluation (interview guide for teacher).

Axis	Thematic inputs	Follow-up questions
***Acceptability*** *(involvement*, *relevance)*	How did the teacher find out about the project? How did he become a volunteer? What motivated him to take part in Epidaure Market? Did his motivation remain the same throughout the sessions?	What information was provided about the project and how was it transmitted? Hierarchical aspect? Had the teacher identified a need among the students? Was the project’s digital, fun aspect a lever?
** *Implementation* ** *(adaptation / fidelity)*	How were the sessions organised? What were the obstacles and levers, both internal and external to the intervention, during its implementation?	Adaptation/adjustment of certain sessions (form, content)? Facilitators or obstacles of a material (e.g. digital resources) or human (classroom climate) nature?

The major themes addressed will be the motivations for involvement, the facilitators and obstacles to intervention (e.g. conditions of access to supports and materials), and the conditions for implementation (acceptability, adaptation and fidelity of the intervention).

The process analysis will be carried out in the Montpellier and Dijon areas. Focus groups and semi-structured interviews will be carried out after the intervention. It is planned to carry out (i) 10 focus groups with pupils; (ii) 20 semi-structured interviews with teachers; (iii) 15 semi-structured interviews with parents of certain pupils in the experimental group, by means of a telephone interview; (iv) 10 semi-structured interviews with school management staff and the Rectorat. This forecast may be subject to change depending on access to the population in the field. Saturation, which depends on the heterogeneity and richness (quality) of the sample, as well as on the quantity of data [66], should be reached in view of the number of interviews envisaged, which is higher than recommended [67].

*Transferability analysis*. The ASTAIRE grid [68] will be used to understand the environmental factors that can influence the effects of the intervention, the methods of implementation and the means to support transfer. The ASTAIRE tool is aimed at researchers and practitioners in the field. It is made up of 2 grids: the first contains 18 criteria and the second 23, which can be classified into 4 categories: population, environment, implementation conditions, transfer support. This second tool will be used, i.e., after the implementation of the "daughter" intervention (defined as "the result of transferring an intervention that has already been tested/implemented in another context"). This grid 2 will help to evaluate a posteriori what may have generated a difference in effects between the parent intervention and the daughter intervention.

To assess the transferability and scalability of public health intervention research [52], it is necessary to identify the key elements of interventions and to take into account the context, particularly from a perspective of combating social inequalities in health. To do so, the FIC (key Functions, Implementation, Context) model [57] will be used to understand how the intervention works and to highlight the transferable theoretical elements that underline the activities implemented in a particular context, while taking into account the new context in which they can be implemented (from Montpellier to Dijon area).

The FIC model allows to structure the description of public health interventions along the lines proposed in the "Out of control" randomized trial model [69]. The model is part of the theoretical framework of population health intervention research (PHIR) [70]. The FIC model [71] has three main objectives: to improve the transferability of interventions, by distinguishing their transferable dimensions (key functions) from context-specific activities (forms); to deconstruct an intervention with the aim of describing it in detail, by identifying its key functions, which could then potentially be transferred to other contexts; to better anticipate and analyze the effects of an intervention on social inequalities in health, through this deconstruction. Key functions represent dimensions of the intervention that are potentially transferable. Forms (theoretical form as conceived by the project leaders or in case of first implementation; observed form in case of transferability which can vary under the effect of the context) refers to the practical implementation of key components through specific activities [71], which facilitate the adaptation of an intervention and enabling similar outcomes in another context. Implementation is the process from key function (recurring element) to theoretical form (adapted according to context). It is a set of activities enabling key functions to be implemented in a particular context [72]. Context influences the implementation of an intervention and affects its outcomes. It constitutes a set of interactions between actors and the environment, enabling (or not) change. It encompasses various dimensions (social, geographical, political). Thus, it contributes to structuring, modifying, facilitating and constraining the intervention, and can influence key functions and the impact of the intervention on social inequalities and to propose recommendations for taking them into account.

A qualitative multi-stage methodology is used to achieve the FIC’s objectives. This involves to participate in project meetings; reading and analyzing documents produced as part of the intervention (minutes of meetings, responses to calls for projects, documents provided to people implementing the intervention, teaching guide); carrying out bibliographical research on the intervention’s themes (sociology of childhood, socio-anthropology of food) as well as on social inequalities in health; conducting (transcribing and analyzing) focus groups or interviews with project stakeholders (members of the research team involved in the project, as well as with those implementing the intervention, mainly teachers and researchers; and, lastly, developing key functions thanks to the literature review and cross-referencing of data from all of the materials.

The FIC interviews guide is based on three main items: stage of intervention and the role of stakeholders; difficulties encountered and factors facilitating; social inequalities in health. These themes are also based on the context of expansion of intervention, the evolution of tools of intervention and their impact on inequalities, and handover between old and new research team members. Interviewees are recruited, as far as possible, taking into account the diversity of their social profile (in terms of gender, age, social class, etc.) from an intersectional perspective, and their role in the deployment of the intervention. The FIC study does not require a large number of interviews and the FIC interviews/focus groups are conducted during or after those of the implementation study.

This model will be adapted here for an analysis of the impact of interventions aiming at improving the food choices (balanced and sustainable) of middle school students, in two different French areas (Montpellier and Dijon academies), while documenting the conditions of its transferability to other regions and with other audiences (profiles of children). FIC interviews and focus groups are conducted with Montpellier research team members (N = 4) and teachers (N = 6 to 7) and with Dijon research team members (N = 3) and teachers (N = 2). A focus group could include teachers from both areas. Interview(s) with Montpellier academy member(s) (rector) could be conducted jointly by a researcher in charge of the FIC and a member of the Montpellier research team.

The ASTAIRE tool and the FIC approach are two different but complementary approaches [53, 57, 73, 74]. The FIC approach does not aim to determine the "active ingredients", i.e. the components that are essentially effective, but rather to distinguish the transferable theoretical processes which are faithful to the intervention, from the adaptable aspects of any intervention implemented. The mobilization of the ASTAIRE and FIC tools requires the collaboration of the main stakeholders involved in the design and implementation of the program; both approaches make it possible to deconstruct the intervention, to distinguish the form and key functions of it—the fixed and variable aspects- to support transferability.

### 2.8 Ethical approval and consent to participate

As part of the project entitled Epidaure Market: evaluation of the effectiveness and transferability to other schools of an intervention to improve balanced and sustainable food choices by schoolchildren, this study was approved by the research ethics committee of Université Paul Valéry—Montpellier 3 (IRB00013307- 2022–14). The electronic database used to carry out this research will comply with the recommendations of the CNIL in accordance with French law no. 78–17 of January 6 1978 on data processing, data files and individual liberties, amended by law no. 2004–801 of August 6 2004.

A letter of information, accompanied by a non-objection form to participate in the study, will be sent to the pupils’ legal representatives at least one month before the start of the intervention. This information document will explain in comprehensible terms the research objectives, design and procedures, as well as their right to refuse to participate in the study or to change their mind at any time without justification or prejudice.

Student anonymity is guaranteed by participant code. In practice, school staff will never have access to students’ answers, and the research team will never have access to students’ names.

For semi-structured interviews and focus groups, a request for consent to audio recording will be made. Anonymity will be guaranteed by assigning fictitious names, and verbatims will be anonymized if personal data is indicated during interviews. There will be no indication of the respondent’s identity.

## 3. Data analysis plan

### 3.1 Analysis of quantitative data

As the sample is made of clusters (classes) that create a correlation between the individual measures, we will consider an analysis in two stages that will use as unit of analysis the cluster (class nested in the school).

For the primary outcome measure, a cross-sectional analysis using a mixed regression model with a random constant for the class effect. More specifically, a logistic regression model will be used on the dichotomous variables. We will also measure the associated intra-class correlation coefficients. A mixed linear regression model will be used for secondary analyses, when continuous variables are involved.

Finally, additional analyses will be carried out to verify the potential effect of socio-demographic characteristics, within the same area, and between the two areas.

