### 2.3 Number of subjects required

The primary outcome is defined as the proportion of students who improve their motivation to healthy sustainable food choices. By assuming a proportion of 5% in the control group (due to slight variation, independent of intervention), a type I error at 5% and a variation coefficient of cluster size of 50% (because class sizes can vary between 20 and 30), 36 clusters with 25 subjects in each group (control and intervention) allow to achieve 90% power to detect a difference between 5.0% and 11.5% in the proportion of students who improve their motivation to choose good food, by varying the intra-cluster correlation between 0.02 and 0.2. A 10% attrition effect was allowed for. To compensate for this loss, more classes were recruited for each area.

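### Section 3.1 describes a two-stage, class-as-unit analysis but names a pupil-level mixed logistic model for the primary outcome, and that model omits the school within which classes were randomised

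*Protocol article*

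**What the plan says.** Section 3.1 of the protocol article makes two statements about the quantitative analysis.

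- The general statement, covering all quantitative data: "we will consider an analysis in two stages that will use as unit of analysis the cluster (class nested in the school").
- The specific statement, one paragraph later, which concerns the main endpoint: "For the primary outcome measure, a cross-sectional analysis using a mixed regression model with a random constant for the class effect". It adds that "a logistic regression model will be used on the dichotomous variables".

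Section 2.7.1 defines the primary outcome per pupil, by "comparing the proportion of students who improved their post-intervention parameters in the intervention and control groups". Section 2.3 plans "36 clusters with 25 subjects in each group (control and intervention").

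Section 2.5 says that classes are randomised with stratification by middle school, balanced between the arms, and that the same science teacher has both experimental and control classes. The article does not say how the two statements in Section 3.1 fit together, and the named model has no school term.

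**The concern.** Read literally, a two-stage analysis with the class as unit first reduces each class to a summary and then compares 36 summaries with 36. A logistic model with a random class intercept is fitted in one step to pupils, and the class is a random effect rather than the unit of analysis. The two differ in weighting and in effect measure: a difference in mean class proportions against an odds ratio conditional on class. One description cannot cover both.

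The second part concerns precision. The opening sentence recognises that classes are nested in schools, and the randomisation uses that structure by balancing the arms within each school. School and teacher differences therefore largely cancel from the comparison between arms. A model with a class effect only does not know this. It counts school differences as part of the class-to-class noise and carries them into the standard error of the treatment effect. What is at stake is precision that the design has already secured.

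**Working it through.** **1. The plan's own figure.** Inputs from Section 2.3: control rate 5%, type I error 5% (two-sided assumed), 36 classes of m = 25 per arm, cluster-size CV 50%, ICC 0.02 to 0.2, 90% power.

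- Design effect: DE = [1 + (m − 1)·ICC] / [1 − CV²·L·(1 − L)], with L = m·ICC / (m·ICC + 1 − ICC).
- ICC 0.02: L = 0.5/1.48 = 0.338, DE = 1.48/0.944 = 1.568, effective n = 900/1.568 = 574.1 per arm, detectable difference 5.04 points.
- ICC 0.2: L = 5/5.8 = 0.862, DE = 5.8/0.970 = 5.978, effective n = 150.6 per arm, detectable difference 11.49 points.

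The stated 5.0 and 11.5 points reproduce if they are read as differences. The sample size is not in dispute. It does not show which analysis is meant.

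**2. Does the choice of analysis matter?** Simulation: 36 classes per arm, 20 to 30 pupils each, beta-binomial class effects (assumed), 500 trials per scenario. A t-test on class proportions was compared with a likelihood-ratio test from the random-intercept logistic model.

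| Rates | ICC | Power, class t-test | Power, mixed model | Verdicts differ at 5% |
|---|---|---|---|---|
| 5% v 10% | 0.02 | 87.2% | 88.8% | 2.0% |
| 5% v 8% | 0.02 | 58.8% | 60.6% | 2.2% |
| 5% v 11.5% | 0.1 | 77.8% | 83.8% | 8.8% |
| 5% v 14% | 0.2 | 79.4% | 87.4% | 14.0% |

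Monte Carlo standard errors are about 1.5 to 2.2 points on power. On the 14.0% it is √(0.14·0.86/500) = 1.6 points. The share of differing verdicts depends on the effect size as well as on the ICC, so 14% is the largest value among these scenarios and not a bound.

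**3. What does leaving out the school cost?** Let p be the rate, ρ the ICC on the scale of proportions, and s the share of between-class variance that lies between schools. The article gives no value for s.

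- Variance of a class proportion as the class-only model sees it: p(1 − p)·[ρ + (1 − ρ)/m].
- Variance relevant to a comparison balanced within schools: p(1 − p)·[(1 − s)ρ + (1 − ρ)/m].

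With p = 0.08, ρ = 0.10, s = 0.5 and m = 25 (all but m assumed):

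- Class only: 0.0736·(0.10 + 0.036) = 0.0736·0.136. The standard error of the difference between arms is √(2·0.0736·0.136/36) = 2.36 points.
- With school: 0.0736·(0.05 + 0.036) = 0.0736·0.086. The standard error is √(2·0.0736·0.086/36) = 1.88 points.
- Ratio: √(0.136/0.086) = 1.26. The 95% half-widths are 4.62 and 3.68 points.

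The rate p cancels from the ratio. Range over the assumptions:

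- ρ = 0.02, s = 0.5: √(0.0592/0.0492) = 1.10.
- ρ = 0.10, s = 0.25: √(0.136/0.111) = 1.11.
- ρ = 0.20, s = 0.5: √(0.232/0.132) = 1.33.
- s = 0: ratio 1, no loss.

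If the ICC of 0.10 is taken on the latent logit scale, the class variance is 3.29·0.1/0.9 = 0.366, the sampling variance is 1/(25·0.0736) = 0.543, and the ratio is √(0.909/0.726) = 1.12.

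**The case against.** The strongest reply is that the article names one analysis for the primary outcome. The two-stage sentence is a general opening that never mentions that outcome. Its reference to nesting, followed by a random constant and intra-class correlations, suggests that two-level was meant. No class summary, weight or t-test appears anywhere. This largely stands, and it rules out several stronger readings that a reader might infer.

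- **That the primary test is not fixed, or that the analyst may choose between two results after seeing both.** The text does not support this, because the specific sentence assigns the mixed model to the primary outcome.
- **That a class-level analysis would be unreliable at a 5% rate because many classes have no improver.** Such classes would be common (0.95²⁵ = 0.277 even without clustering). That is fatal only to an analysis of class log-odds, which the article does not propose. A t-test on class proportions, simulated under no effect at 5%, had a type I error of 5.1%, 4.7% and 4.5% at ICC 0.02, 0.10 and 0.20.
- **That a risk difference must be reported because the power statement uses proportions.** Logistic regression after a power calculation on proportions is routine, and supplementary effect measures may be left to the SAP.

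It can also be said that stratification terms are often left to the SAP. Here, however, the article states the model's structure, with a class effect only. An SAP that follows it would omit the school. Nor does the reply rescue the opening sentence: even if two-level was meant, the class is not the unit of analysis in a pupil-level model.

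**Conclusion.** The point holds as a correction to wording and model, of moderate weight. The opening sentence of Section 3.1 does not describe the model named for the primary outcome, and the two analyses it could denote can lead to different verdicts, in 2% to 14% of simulated trials. That range rests on assumed beta-binomial class effects and class sizes. The power gap in the simulation should not be read as a merit of the mixed model, because its type I error was not assessed there.

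The omission of the school is the part with a real cost. The standard error is about 25% too large in the worked example, roughly 10% to 33% too large over the other proportion-scale cases with a school share of 25% or 50%, and unaffected if schools do not differ. The share of variance between schools is an assumption throughout. A reader might infer that leaving out the school threatens a false positive result. It does not: with arms balanced within schools the error is conservative, so the loss is in precision and power.

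**What to change.** Replace the opening of Section 3.1, and carry the same text into the SAP:

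- Delete the sentence on two stages and the cluster as unit. If a class-level comparison is wanted, label it a sensitivity analysis.
- State one primary analysis: a pupil-level mixed logistic model for improvement, with arm, a school (stratum) term and a random intercept for class within school. Say whether the school term is fixed or random. A random intercept is the safer choice if some schools contribute few improvers.

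The cost is two sentences. No new data are needed, because the participant code in Section 2.5 already contains the school and the class. The sample size does not change.
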